### Statistical Analysis

Descriptive analysis will be performed for all variables to characterize the sample. For continuous variables, mean, SD, median, and range values will be calculated. For categorical variables, absolute and relative frequencies will be used to describe the data [29-31].

Normality will be studied using the Kolmogorov-Smirnov and Shapiro-Wilk tests. The effect of using the PC4L system will be analyzed by applying the paired-sample *t* test (2-tailed) and the Wilcoxon signed rank test to each variable (statistical significance will be set at P<.05).

The Pearson and Spearman correlation tests will be used to validate the PC4L systems metrics (statistical significance will be set at P<.05).

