### Aims

This study represents the third, and last, phase (pilot 3) of large-scale pilots aiming to gradually co-design and iteratively test the PC4L integrated platform and modules.

While pilot phases 1 and 2 focused on technical feasibility and patients’ satisfaction, this protocol focuses on the following objectives:

To assess the impact of using the PC4L platform on patients’ quality of lifeTo compare the metrics generated by the PC4L platform in real-life conditions with the clinical outcome measuresTo evaluate the feasibility and safety of measuring disease progression and patient health status through the global functioning of the PC4L systemTo assess and compare the feasibility and usability of 2 different versions of the PC4L system (fully equipped version vs cloud-based solution)To increase patients’ safety and empowerment

As the primary outcome, the study will provide:

The difference in quality of life between groups (experimental vs control group), measured by the EQ-5D-3L scale at the end of the study

The following secondary outcomes will also be acquired:

The correlation coefficient of the PC4L platform metrics (eg, steps and physical activity levels, sleep, number of falls, cognitive scores) with the clinical outcome measures (eg, motor clinical evaluation, sleep questionnaire, Falls Efficacy Scale-International [FES-I], cognitive evaluations) measured at baseline, end of the study, and the values of change from baselineSystem usability assessment, measured through the System Usability Scale (SUS), at the end of the studyUsers’ satisfaction with the PC4L system, measured through a 5-point Likert Scale, the mHealth User Satisfaction Questionnaire, and the participants’ answers to open questions, at the end of the studyChanges in patients’ satisfaction and empowerment, measured by the Patient Assessment of Chronic Illness Care (PACIC) and the Short Assessment of Patient Satisfaction (SAPS) scales, respectively, at baseline and at the end of the studyChange in patients’ use of medical resources (number of admissions and number of days spent in health institutions) in the last month, measured at baseline and at the end of the study

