### Randomization

Patients were randomized in a ratio of 1:1 to the intervention group (use the PC4L system) or the control group (no intervention) by an independent, nonclinical partner of the project consortium.

Patients allocated in the intervention group were randomized in a ratio of 3:1 to the “cloud-based solution” and the “fully equipped” PC4L system version.

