#### Quality of Life Assessment

The primary outcome of the study will be the difference in quality of life between groups, measured by the EQ-5D-3L scale [24], before and after the experimentation.

The EQ-5D-3L descriptive system comprises 5 dimensions, namely, mobility, self-care, usual activities, pain/discomfort, and anxiety/depression. Each domain was scored by patients through 3 levels: no problems (1), some problems (2), and extreme problems (3) in the execution of the specific item.

Quality of life data were analyzed using dedicated spreadsheet files.

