### Sample Size

According to published evidence [27], the minimal clinically important difference using the EQ-5D-3L in patients with PD is 5.23 points. The sample size calculation was based on these values and on the data provided in a previous study [28] in the PD field that compared the quality of life of 2 groups of patients, resulting in 10% of difference between groups, corresponding to 6 points. It was estimated that 558 patients, 279 per study group, are necessary to improve 10% in the EQ-5D-3L score, with 95% power. Dropouts were not considered in the calculation. Based on this result, the number of participants was distributed among clinical centers, according to their recruitment capacity (Table 2).

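### The article names only paired before/after tests for the PC4L effect, although the primary outcome and the sample size concern a difference between randomised groups

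*Protocol article*

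**What the plan says.** The design is a parallel-group randomised trial. Under Randomization: "Patients were randomized in a ratio of 1:1 to the intervention group (use the PC4L system) or the control group (no intervention").

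The Aims section gives the primary outcome as "The difference in quality of life between groups (experimental vs control group), measured by the EQ-5D-3L scale at the end of the study". Quality of Life Assessment also makes it a between-group difference ("The primary outcome of the study will be the difference in quality of life between groups, measured by the EQ-5D-3L scale") but times it differently: "measured by the EQ-5D-3L scale [24], before and after the experimentation".

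The Sample Size section starts from a 10% difference between groups, equated to 6 points, and concludes: "It was estimated that 558 patients, 279 per study group, are necessary to improve 10% in the EQ-5D-3L score, with 95% power".

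Statistical Analysis first says that normality will be examined with two named tests. Its next sentence turns to the intervention: "The effect of using the PC4L system will be analyzed by applying the paired-sample". That sentence goes on to identify Student's procedure for pairs, adds a rank-based counterpart and sets the threshold: "test (2-tailed) and the Wilcoxon signed rank test to each variable (statistical significance will be set at P<.05"). The only other inferential methods are correlations, and they serve another purpose: "The Pearson and Spearman correlation tests will be used to validate the PC4L systems metrics".

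**The concern.** The paired t test and the signed rank test both need paired observations. The article describes no matching of patients across arms, so the only pairs available are the baseline and end-of-study values of the same patient. A test on those pairs asks whether patients changed over time. The primary outcome asks whether the arms differ.

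The two questions separate whenever something other than PC4L moves EQ-5D-3L in both arms, and the article gives reasons to expect that. Table 2 places 204 of 558 patients in the rehabilitation scenario, where the Discussion describes supervised motor and cognitive treatment. The Control Group section says that controls also receive written recommendations. Improvement from these sources would count as a PC4L effect. In the other direction, these are neurodegenerative diseases, and a decline shared by both arms could cancel a real benefit in a before/after test.

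**Working it through.** **1. Is there a between-group test anywhere in the article?**

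| Element | Section | Comparison |
|---|---|---|
| Design | Randomization | two independent arms, 1:1 |
| Primary outcome | Aims; Quality of Life Assessment | between groups |
| Sample size | Sample Size | between groups, 279 per arm |
| Test of the PC4L effect | Statistical Analysis | within patient |
| Correlations | Statistical Analysis | metrics against clinical measures |

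No two-sample t test, rank sum test, ANCOVA, mixed model or group-by-time test is named. This mismatch needs no assumed figure.

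**2. The plan's own figure.** The article gives no SD, so 279 per group cannot be reproduced directly. Solving backwards for a two-group comparison with two-sided 5% and 95% power:

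SD = 6 × √(279/2) / (1.960 + 1.645) = 6 × 11.811 / 3.605 = 19.66.

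With the t distribution in place of the normal, the result is 19.62. I use 19.6. The sample size is therefore compatible with a two-group test, but cannot be verified.

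**3. The paired test when PC4L does nothing.** Assumed: SD 19.6 at both visits, baseline/end correlation r, the same mean change c in both arms, and 279 patients in the PC4L arm.

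- SD of change = 19.6 × √(2(1 − r)), which is 23.19, 19.60 or 15.18 for r = 0.3, 0.5 or 0.7.
- Standard error = SD of change / √279, which is 1.388, 1.173 or 0.909.
- Noncentrality = c / standard error, with 278 degrees of freedom.

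| Common change | r = 0.3 | r = 0.5 | r = 0.7 |
|---|---|---|---|
| 2 points: noncentrality | 1.44 | 1.70 | 2.20 |
| 2 points: P<.05 in the PC4L arm | 30% | 40% | 59% |
| 3 points: noncentrality | 2.16 | 2.56 | 3.30 |
| 3 points: P<.05 in the PC4L arm | 58% | 72% | 91% |

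The SD matters too. At r = 0.5 and 3 points, the rate is over 99% with SD 10 and 52% with SD 25.

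A simulation of 10,000 trials (SD 19.66, r = 0.5, 3 points) gave 72.2% for the paired test. Between-group t tests gave 5.1% on the end-of-study score and 5.0% on change.

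**4. Paired tests in each arm, then comparing P values.** At 2 points and r = 0.5, each arm is significant with probability 0.397, independently of the other. The pattern of PC4L significant and control not then occurs with probability 0.397 × (1 − 0.397) = 0.239. A between-group test at two-sided 5% would favour PC4L in 2.5% of trials.

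**5. A common decline.** If PC4L truly adds 6 points and both arms would otherwise lose 6, the expected change in the PC4L arm is 6 − 6 = 0. The paired test is then significant in 5% of trials. A between-group test of end-of-study scores has about 95% power for the same 6 points.

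**The case against.** **The article is not the whole plan.** A reader might infer that the primary outcome will never be tested and that randomisation is wasted. The documents do not support that. This is a journal article, a fuller protocol or SAP may name a between-group test, three sections state between-group intent, and both arms are measured, so the contrast can still be computed. What stands is narrower. The article does not leave the test open; it assigns the PC4L effect to a family of tests that cannot address the stated outcome. If another document names a between-group test, the published text contradicts it.

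**Paired tests have a legitimate use.** The section does not restrict them to one arm, and some secondary outcomes are defined as changes (PACIC, SAPS, use of medical resources). Within-arm description is reasonable there. It does not test an effect against control.

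**Two tests, two chances?** A reader might infer that either test may be declared the winner, inflating the error rate. The preceding sentence on normality makes the ordinary reading a choice between them. The selection rule is loosely worded, nothing more.

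**Regression to the mean.** It is tempting to add this to the sources of common change. No entry criterion selects on poor quality of life, so the documents give it no support.

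**The size is illustrative.** SD, correlation and common change are all assumed. Rehabilitation patients are 204/558 = 36.6% of the sample. If gain arose only there, an arm-wide 2 or 3 points would need about 5.5 or 8.2 points in those patients, above the 5.23 points the article cites as clinically important. Decline in the others could offset it. This limits the figures but not the mismatch.

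**Outcome wording.** Both statements are between-group, and under randomisation end-score and change contrasts have the same expected value. This is a small clean-up.

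**Conclusion.** The point holds and should be corrected before the primary conclusion is drawn. As written, the article tests the PC4L effect within patients, while its design, primary outcome and sample size are between groups. That conclusion rests on the text alone.

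The consequence can be large in either direction. With no PC4L effect and SD 19.6, a common change of 2 to 3 points makes the paired test significant in about 30% to 91% of trials over r = 0.3 to 0.7, against about 5% for a between-group comparison. A common decline can conceal a real benefit. These rates depend on an assumed SD, correlation and common change, none of which the article gives. They show what could happen and do not predict this trial's result.

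**What to change.** Replace the sentence on the PC4L effect with wording such as:

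> Primary analysis: end-of-study EQ-5D-3L score compared between randomised groups by ANCOVA adjusted for baseline EQ-5D-3L, with patients analysed in their allocated group, in all randomised patients with available data. The adjusted difference with its 95% confidence interval and one two-sided P value is the sole basis for the primary conclusion.

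Centre and scenario may be added as covariates. A two-sample comparison of end-of-study scores would also match the Aims section; baseline adjustment is a preference, not a condition for repairing the error.

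Also:

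- Use the same between-group approach for the other outcomes measured in both arms.
- Keep the paired tests as within-arm description only.
- State the primary outcome identically in Aims and in Quality of Life Assessment.
- Say how the analysis set fits the Withdrawal of Participants section, which bars data after withdrawal from being collected or used statistically.

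The cost is mainly wording. EQ-5D-3L is measured at baseline and at the end in all patients, and Table 2 sets out centre and scenario. No further patients are needed for this change under the assumptions above: at SD 19.6 and full follow-up, an end-of-study comparison keeps about 95% power for 6 points. Recruitment is closed, so the change should be fixed and dated in the protocol or SAP before outcomes are compared by arm. If that comparison has already been made, the change should be reported as made afterwards.

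### The effect analysis puts two paired tests on every variable with no deciding test, and neither test estimates the between-group EQ-5D-3L difference that is the primary outcome

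*Protocol article*

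**What the plan says.** The Statistical Analysis section first states that "Normality will be studied using the Kolmogorov-Smirnov and Shapiro-Wilk tests". No consequence of that check is given. It then says that the effect of using the system will be analysed by a two-tailed paired t test and "the Wilcoxon signed rank test to each variable", with one significance threshold, P<.05, for both. It does not say which test decides when they differ, or whether one or both must be significant.

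The primary outcome is defined in two places, both times as a contrast between arms. The Aims section gives "The difference in quality of life between groups (experimental vs control group), measured by the EQ-5D-3L scale at the end of the study". The Quality of Life Assessment section says "The primary outcome of the study will be the difference in quality of life between groups", and adds that it is measured before and after.

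On the type of data, the Quality of Life Assessment section describes five dimensions and says "Each domain was scored by patients through 3 levels". It does not say whether a sum, an index or another EQ-5D-3L score is analysed. The Sample Size section works with differences of 5.23 and 6 points, 279 patients per group and 95% power.

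**The concern.** A trial sized for a confirmatory answer on one outcome needs one analysis that gives that answer. This section supplies two P values for the same variable and no order between them. The two tests address different hypotheses: the t test concerns the mean change, and the signed rank test concerns symmetry of the changes about zero. With skewed changes they can part company, and the conclusion is then open to choice after the data are seen.

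A more basic problem sits in the same sentence. A paired test asks whether patients changed over time. It takes in natural progression, rehabilitation given to everyone, regression to the mean and the effect of being studied. Randomization was done to remove these, and a paired test does not use it. The primary outcome as defined would have no test, and a significant before-after change in the intervention arm could be reported as an effect of the system.

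**Working it through.** **Inputs from the article.** Threshold P<.05, two-tailed t test; both tests paired (Statistical Analysis). 279 per group, 95% power, differences of 5.23 and 6 points (Sample Size). Five 3-level dimensions (Quality of Life Assessment). The article gives no SD and no distribution of change, so everything below that needs one is an assumption.

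**The plan's own figure.** The 558 can be neither reproduced nor refuted, because no SD is stated and the Sample Size section gives no alpha. It can be inverted. With two-sided alpha .05, SD = d × √(n/2) / (1.960 + 1.645):
- d = 6: 6 × √139.5 / 3.605 = 19.66
- d = 5.23: 5.23 × √139.5 / 3.605 = 17.14

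Either way the trial is sized on a mean difference between two groups, with a standardized effect of 6 / 19.66 = 0.305.

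**Step 1: two P values.** Paired differences were simulated under a symmetric null, n = 279, 8,000 runs per row, Monte Carlo SE about 0.25 percentage points.

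| Assumed change | t test | Signed rank | Either | Both | Chosen by Shapiro-Wilk |
|---|---|---|---|---|---|
| Normal | 5.4% | 5.2% | 6.3% | 4.3% | 5.6% |
| Heavy-tailed (t, 3 df) | 4.7% | 4.8% | 6.9% | 2.6% | 4.8% |
| Heavy-tailed (Laplace) | 5.4% | 5.1% | 7.2% | 3.3% | 5.1% |
| Sum-score-like | 4.9% | 5.2% | 5.8% | 4.3% | 5.2% |
| Index-like | 5.1% | 5.2% | 6.5% | 3.9% | 5.2% |
| VAS-like | 5.0% | 5.1% | 5.8% | 4.2% | 5.1% |

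Only the rule that either P value counts exceeds 5%. The excess is well short of the 1 − 0.95² = 9.75% for two independent tests, because the two tests are highly correlated. A two-arm version (t test and rank-sum test, 279 per arm, same distribution in both arms, 6,000 runs) gave about 5% for each test. Either test was significant in 6.0% of runs with normal changes, 7.4% with heavy tails (t, 3 df) and 6.7% with a skewed discrete change.

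**Step 2: normality as the selector.** With the assumed EQ-5D-like changes at n = 279, Shapiro-Wilk rejected in 100% (sum-score-like), 99.5% (index-like) and 88.5% (VAS-like) of runs. Selection would therefore very likely lead to the signed rank test. That keeps the error near 5% under a symmetric null, but it does not estimate the 5.23 or 6 points on which the trial was sized.

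**Step 3: paired tests against a between-group outcome.** Suppose, for illustration, that both arms change by 3 points over the study, the SD of change is 19.66 and the system has no effect. Then SE = 19.66 / √279 = 1.177 and 3 / 1.177 = 2.55. The chance that a two-sided paired test in one arm is significant is Φ(2.55 − 1.96) ≈ 72%. The true between-group difference is zero. A shared change is not far-fetched: 204 of the 558 places in Table 2 (37%) are in rehabilitation, where patients in both arms are under treatment.

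**The case against.** The strongest reply is that this is a condensed article. Normality tests followed by a parametric and a rank-based test is familiar shorthand for letting normality choose, and the next paragraph pairs Pearson with Spearman in the same way. On that reading there is one P value, and the table shows its error near 5%. Which test decides is also commonly left to a full protocol or SAP, neither of which is shown. This stands against two stronger readings.

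A reader might infer that the plan's error rate necessarily exceeds 5%. The text does not support that. It needs a rule that either result suffices, which is not stated; if both had to be significant, the rate would be 2.6% to 4.3%. Nor should large rejection rates of the signed rank test for skewed changes with mean zero be cited as inflation. Such changes violate that test's own null of symmetry, and they concern one arm over time. In a two-arm comparison with equal distributions, each test returns to about 5%.

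A reader might also infer that EQ-5D-3L is bound to fail the normality tests. That is likely but not established, because the article does not fix the score. A 10% difference equal to 6 points implies a base of 6 / 0.10 = 60, which a sum of five items scored 1 to 3 (range 5 to 15) cannot reach.

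The reply does not reach the third step. The article is not silent on the effect analysis. It names the tests, and both are within-patient.

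**Conclusion.** The point holds in this form: two paired tests on each variable, no deciding result for the primary outcome, and neither test estimating the between-group difference that the article itself defines. The mismatch between paired tests and a between-group outcome is the heavier part and rests on the text alone; the 72% only illustrates it, under an assumed 3-point common drift and an assumed SD. The multiplicity part is modest, about 6% to 7.5% if either P value may be claimed and about 5% if normality selects, under assumed null distributions. That normality selection would lead to the signed rank test is very likely rather than certain. The sponsor should correct this before the primary result is reported, because it bears directly on the trial's main conclusion.

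**What to change.** State one deciding analysis for the primary outcome: the between-group mean difference in end-of-study EQ-5D-3L, adjusted for the baseline value (for example ANCOVA), with a 95% CI, and with robust or bootstrap standard errors if non-normality is a worry. Name the EQ-5D-3L score to which it applies. Do not let the Kolmogorov-Smirnov or Shapiro-Wilk test choose the primary test. Keep a rank-based comparison between groups only as a labelled sensitivity analysis that cannot change the conclusion. Before-after tests within an arm may stay as description, but not as evidence of an effect of the system.

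The cost is a change of analysis wording. EQ-5D-3L is already collected at baseline and at the end in both arms, so no new data, visits or patients are needed. At about 279 per arm a mean-based comparison is robust to non-normality, so little is given up.

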### Recruitment

Patients with PD and other parkinsonian syndromes, AD, or ODs were invited to participate from the clinical centers involved in the study. Each participant organization was assigned to recruit a number of participants related to their skills, experience, number of researchers involved, and access to users (Table 2).

**Table 2 table2:** Distribution of participants per clinical center and scenario.

Scenario/clinical center	Rehabilitation (n=204), n	Day care (n=82), n	Home (n=272), n	Total (N=558), n
APM^a^	80	N/A^b^	26	106
CCP^c^	63	N/A	62	125
CNS^d^	46	N/A	86	132
UHB^e^	15	N/A	15	30
UMF^f^	N/A	30	30	60
WBW^g^	N/A	52	53	105

^a^APM: Asociacion Parkinson Madrid.

^b^N/A: not applicable.

^c^CCP: Casa di Cura del Policlinico.

^d^CNS: Campus Neurológico Sénior.

^e^UHB: University and Emergency Hospital of Bucharest.

^f^UMF: University of Medicine and Pharmacy.

^g^WBW: Wohlfahrtswerk für Baden-Württemberg.

To reach the planned number of recruits, many strategies were implemented: participants were contacted through online webinars; through brochures placed in specific centers such as pharmacies, leisure centers, and medical offices; and through patients’ associations. Further, regular updates were posted via online newsletters on different websites, such as the PC4L website and end users organizations’ websites. In addition, information about the PC4L pilot 3 study was shared during national and international conferences. Recruitment was also promoted in a collaborative way thanks to partners from other European projects. Finally, participants were recruited in person when accessing the medical facilities and via phone contact or emails after searching local databases.

Patients who discontinue the study participation because of medical conditions (ie, infections, falls, medical emergencies) or unwilling to participate any longer for other reasons (ie, difficulty with technology, loss of interest) will be considered dropouts.

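### The effect of PC4L is to be tested only within patients, although the primary outcome is a between-group difference; a baseline-adjusted between-arm model with centre, scenario and diagnosis should replace these tests

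*Protocol article*

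**What the plan says.** Aims gives the primary outcome as "The difference in quality of life between groups (experimental vs control group), measured by the EQ-5D-3L scale at the end of the study". Quality of Life Assessment also describes a difference between groups, there before and after the experimentation.

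For the effect analysis, Statistical Analysis first names a two-tailed t test on paired data ("The effect of using the PC4L system will be analyzed by applying the paired-sample"). Its second method is given as "Wilcoxon signed rank test to each variable (statistical significance will be set at P<.05". It names no other method for the effect of the system. The only further tests are normality tests and the correlations used to validate the platform metrics.

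Sample Size plans for a contrast of two groups: "It was estimated that 558 patients, 279 per study group, are necessary to improve 10% in the EQ-5D-3L score, with 95% power". The target is described as "resulting in 10% of difference between groups, corresponding to 6 points", and it is also stated that "the minimal clinically important difference using the EQ-5D-3L in patients with PD is 5.23 points".

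On recruitment, "Each participant organization was assigned to recruit a number of participants related to their skills, experience, number of researchers involved, and access to users". The resulting distribution over centres and scenarios is in Table 2. Patients have PD or another parkinsonian syndrome, AD, or another dementia. On allocation, "Patients were randomized in a ratio of 1:1 to the intervention group (use the PC4L system) or the control group (no intervention"; stratification is neither stated nor excluded.

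**The concern.** The trial is randomised and sized for a contrast between arms, but the stated tests do not form one. A paired test in the PC4L arm asks whether those patients changed. Testing each arm separately and comparing the two P values does not test the difference either.

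This matters here because change unrelated to PC4L is plausible in both arms. Of 558 patients, 204 (37%) are in rehabilitation, where the Discussion describes personalised motor and cognitive treatment regardless of arm. The control group receives written recommendations. The diseases are progressive. A shared improvement would be credited to the system, and a shared decline could hide a benefit.

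Second, the population is mixed by design. Scenario also determines follow-up length (up to 3 months at home and in day care, length of stay in rehabilitation), and the fully equipped version is used only in rehabilitation. Centre, scenario and diagnosis are known for every patient, but the named tests have no place for them.

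**Working it through.** **1. Number of cells (Table 2).** Rehabilitation 80 + 63 + 46 + 15 = 204; day care 30 + 52 = 82; home 26 + 62 + 86 + 15 + 30 + 53 = 272; total 558. There are 12 filled cells of 15 to 86 patients. Each centre has home patients and one other scenario, so centre and scenario terms can be estimated together.

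**2. The plan's own sample size.** No SD is stated, so 279 per group cannot be reproduced directly. Solving the two-sample normal formula for the SD:

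SD = difference x sqrt(279/2) / (1.960 + 1.645)

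- 6 points, two-sided 5%: SD = 6 x 11.81 / 3.605 = 19.66
- 5.23 points, two-sided 5%: SD = 17.14
- one-sided 5%: 21.54 (6 points) or 18.78 (5.23 points)

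For scale, 6 points with an SD of 15, 20 or 25 would need 163, 289 or 452 per group. I use 19.66 below, as an assumption.

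**3. What the stated tests do when PC4L has no effect.** Both arms were given the same mean change, with an SD of change of 19.66 (assumption) and 279 per arm, in 4,000 simulated trials per row.

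| Common change (points) | Paired t test, PC4L arm: significant | Two-sample t test on change: significant |
|---|---|---|
| 0 | 5.3% | 5.6% |
| 1 | 14.5% | 5.1% |
| 2 | 39% | 5.6% |
| 3 | 73% | 5.1% |
| 4 | 92% | 5.3% |

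**4. Whether mixed cells harm the stated tests.** Stable differences in level cancel in a within-patient difference. With a cell-level SD of 15 and a within-patient SD of 14 at each visit (assumptions, 2,000 simulated trials), the SD of the PC4L arm's mean change was 1.20. The value expected with no cell effect is 14 x sqrt(2/279) = 1.19. Change that depends on scenario does not cancel in this way.

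**5. What centre, scenario and diagnosis add to a between-arm comparison.** Let these terms explain a share R2 of the variance (not in the documents; assumed range 0.05-0.20). Then SE = 19.66 x sqrt(1 - R2) x sqrt(2/279), and power = Phi(difference/SE - 1.960). The few degrees of freedom used are ignored.

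| R2 | SE | Power at 6 points | Power at 5.23 points | Per arm for 95% at 6 points |
|---|---|---|---|---|
| 0 | 1.664 | 95.0% | 88.1% | 279 |
| 0.05 | 1.622 | 95.9% | 89.7% | 266 |
| 0.10 | 1.579 | 96.7% | 91.2% | 252 |
| 0.20 | 1.489 | 98.1% | 94.0% | 224 |

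If 5.23 points was the design target, the implied SD is 17.14 and the 5.23-point column becomes the 6-point column.

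**6. If allocation was balanced within cells (not stated).** An unadjusted between-arm test would then use too large an SE. Its type I error would be 2 x (1 - Phi(1.960/sqrt(1 - R2))): 3.9% at R2 = 0.10 and 2.8% at R2 = 0.20.

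**The case against.** The strongest defence is that this is a journal article. Covariate lists, stratified analyses and details of randomisation usually stand in the full protocol or analysis plan, which are not shown. An unadjusted comparison in a 1:1 randomised trial is valid. On this view, missing terms for centre, scenario and diagnosis are an omission of no consequence, and asking for them is a preference.

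That stands for the covariates taken alone. It does not cover the choice of test. The article does not leave the effect analysis open: it names two tests, both within-patient, for an outcome that it defines between groups.

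A reader might also infer two stronger points, and neither is supported.

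- One is that the spread over 12 cells inflates the error of the stated tests. It does not, because stable levels cancel (step 4).
- The other is that chance imbalance in the mix of settings would bias the effect estimate. The stated tests give no between-arm estimate for it to enter. In an unadjusted comparison under simple randomisation, such imbalance is ordinary sampling error, already inside the SE of 1.664. At R2 = 0.10 that component is 19.66 x sqrt(0.10) x sqrt(2/279) = 0.53 points, and 1.579² + 0.53² gives back 1.664². Under balanced allocation the unadjusted test errs on the cautious side.

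**Conclusion.** The point holds: the stated analysis of the PC4L effect does not test the primary outcome. This conclusion comes from setting Statistical Analysis beside Aims, Quality of Life Assessment and Sample Size, and needs no assumption. How far a paired test can mislead depends on the change common to both arms, which is unknown. At the assumed SD of change, 1 to 4 points of shared change gives 14.5% to 92% significant results with no effect of PC4L.

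Adjustment for centre, scenario and diagnosis is the smaller part. It is worth about 1 to 3 points of power at 6 points and 2 to 6 at 5.23 points. Those figures rest on a back-solved SD and an assumed R2; the documents give neither. The documents do not show that randomisation was unstratified, or that the full analysis plan lacks a between-arm comparison.

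**What to change.** In Statistical Analysis, for the primary outcome, replace the paired t test and the signed rank test with a between-arm linear model. The response is end-of-study EQ-5D-3L. The terms are arm, baseline EQ-5D-3L, centre (6), scenario (3) and diagnosis group. Report the adjusted difference between arms with its 95% confidence interval. With baseline in the model, the arm effect is the same for the end score and for change from baseline, so this serves the wording in both Aims and Quality of Life Assessment. Within-patient tests may stay as description of each arm, labelled as such.

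The cost is wording only. Study Assessments has EQ-5D-3L measured in all patients at both time points, and the three factors are known at entry, so closed recruitment is no obstacle. Centre, scenario and diagnosis use about 5 + 2 + 2 = 9 degrees of freedom out of 558, taking diagnosis as three groups. The change should be made and dated before the between-arm results are seen.
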